## Abstract

The purpose of this research is to evaluate the feasibility, acceptability, and preliminary efficacy of a household food-waste prevention and minimization intervention, titled the Culinary Home Empowerment for Food Waste Prevention and Minimization (CHEF-WPM), which consists of a culinary education video series for home cooks. The specific aims are to (1) assess the effects of the intervention at a population level across process (feasibility, usage, acceptability, satisfaction) and preliminary efficacy (motivation, opportunity, ability) metrics and (2) assess the effects of the intervention at a community level across process (feasibility, usage, acceptability, satisfaction) and preliminary efficacy (motivation, opportunity, ability, household food waste, sustainable dietary practices) metrics. The intervention includes eight modules, each containing three to five brief videos, as well as downloadable recipes and worksheets. The evaluation will explore the effects of the program through two distinct investigations, namely (1) voluntary access to the intervention content in a population-based setting and (2) intensive delivery of the intervention content as part of a remote class in a community setting. Evaluation of the intervention in the population-based setting will use a single-arm, quasi-experimental post-test only study design. All home cooks who access the videos will be invited to answer a five-question post-video survey about acceptability, satisfaction, and potential implementation of the learning. A separate sample of individuals will be recruited to participate in a more in-depth evaluation (pre- and multiple post-test survey). Evaluation of the community-based intervention will use a mixed methods study design. Findings from the two distinct evaluation studies will be jointly discussed and triangulated to support larger conclusions about the intervention’s desirability, impact on motivation, opportunity, ability, and food waste, and the potential directions for further improvement.

## 1. Introduction

As the global population grows, the demand for food is projected to increase by over 50% in the next 50 years, assuming current eating patterns remain unchanged [1]. According to the United Nations Environment Programme (UNEP), one-third of all food produced worldwide is lost or wasted annually [2]. Food waste is the largest component of landfills and incineration streams [3], with the majority occurring at the consumer level [2]. In the U.S., over 60% of food waste occurs at the consumption stage, including households and restaurants [3]. This significant amount of wasted food presents opportunities to combat food insecurity, save energy, and address environmental damage and climate change [3].

Food waste in high-income countries is primarily attributed to consumer behavior and policy. The National Academy of Sciences (NAS) has identified 11 consumer-level drivers of food waste based on the Motivation–Opportunity–Ability (MOA) framework [4]. These drivers include consumer knowledge and skills, goals related to food and nutrition, food preferences and diet, psychological distance from food, food environments, and relevant policies and regulations [4].

Block et al.’s four stages to consumer decisions align closely with the NAS’s consumer-level drivers to food waste, as each stage is significantly influenced by consumer knowledge, skills, and food environments [5]. For example, in the *pre-acquisition stage*, consumer knowledge regarding the safe handling and culinary use of blemished produce can determine whether it will be purchased and used or discarded. Similarly, in the *acquisition stage*, consumers’ ability to accurately calculate purchase amounts helps prevent overbuying food products. During the *consumption stage*, household food environments influence opportunities to avoid food waste by practicing proper food and leftover storage. Finally, in the *disposition stage*, consumer knowledge of food conservation and sustainable practices can reduce a household’s food-waste impact [4,6].

### 1.1. The Consumer Food-Waste Paradox

Despite expressing a dislike for wasting food, consumers often engage in behaviors that result in food waste. To explore this paradox, Le Borgne et al. evaluated consumer concern for food waste and its impact on adopting “waste-prevention routines” [7]. They identified two dimensions of consumer concern: “individual/interpersonal concern”, which strongly influenced waste-prevention behaviors, and “global concern”, which did not have a significant effect. Their findings suggest that effective strategies to reduce household food waste should focus on enhancing individual/interpersonal concerns through economic concerns, food involvement, and food education. Similarly, Romani et al. emphasized the importance of “routine food management” behaviors in preventing food waste and highlighted the potential of targeted educational programs to promote sustainable food practices [8]. Their research indicates that daily food practices (shopping, cooking, and eating) and key behaviors (over-purchasing, poor meal-planning, and improper food storage) significantly contribute to household food waste and should be the focus of educational interventions.

### 1.2. Theoretical Underpinnings of Household Food-Waste Prevention

The Theory of Planned Behavior (TPB) [9] and Triandis’ Theory of Interpersonal Behavior (TIB) [10] have been used to study consumer and household food-waste behaviors. TPB posits that behavior is driven by *attitudes* (e.g., a belief that wasting food is bad for the environment), *subjective norms* (e.g., societal expectations about food waste), and *perceived behavioral control* (e.g., self-efficacy in being able to reduce food waste). Triandis’ TIB expands on TPB by integrating *habit* (e.g., habitual over-purchasing of food), *emotions* (e.g., guilt associated with wasting food), and *facilitating conditions* (e.g., availability of food storage facilities). By integrating these theories into a comprehensive framework, interventions can address both the rational and habitual aspects of food-waste behavior.

The Motivation–Opportunity–Ability (MOA) Model has been viewed as an integration of the Theory of Planned Behavior with Triandis’ Theory of Interpersonal Behavior [11]. The MOA Model offers a targeted framework for understanding and influencing consumer behavior by considering *motivation*, an individual’s desire or willingness to engage in a behavior (e.g., household food-waste prevention); *opportunity*, external circumstances that enable or inhibit the behavior (e.g., access to tools and resources that make it easier to reduce food waste, such as meal planning tools, food storage containers, kitchen utensils); and *ability*, an individual’s capacity to perform the behavior (e.g., skills and knowledge to reduce food waste in the kitchen) (Figure 1) [11]. Adoption of the target behavior builds self-efficacy and reinforces ability and motivation, creating a positive feedback loop. A signature feature of the MOA Model is its integration of motivational, habitual, and contextual factors into a single model that can be used to explain pro-environmental behavior [11].

### 1.3. Cooking Education as a Tool for Reducing Household Food Waste

Cooking education is a crucial tool for reducing household food waste. It enhances individuals’ food agency—the ability to purchase and prepare food within their social, physical, and economic environments—empowering them to achieve their food-related goals [12]. Studies have shown that cooking interventions promote good nutrition and sustainable food practices [13,14,15,16]. Countries like Finland and Australia have incorporated home economics into educational curricula to mitigate food waste and enhance household sustainability [17]. Home economics educates consumers to be thrifty and mindful with food, make informed decisions about resources, and understand the environmental impact of their actions [18].

### 1.4. Specific Aims

While the NAS study provides a host of suggestions to reduce household food waste [4], translating the aforementioned findings into practice at the population and community levels is beyond the scope of most studies. Hence, the protocol described herein tests an approach to translating promising scientific findings into consumer-facing food-waste prevention and minimization lessons. The purpose of this protocol paper is to detail the design and methodology of a household food-waste prevention and minimization intervention titled Culinary Home Empowerment for Food Waste Prevention and Minimization (CHEF-WPM). Consistent with a protocol paper, this paper was submitted before data collection and, as such, does not present results or statistical analysis. Follow-on papers after data collection will do so [19]. The intervention consists of a culinary education video series for home cooks. The aims of the study are to:

Aim 1: assess the effects of CHEF-WPM at a population level across process (feasibility, usage, acceptability, satisfaction) and preliminary efficacy (motivation, opportunity, ability) metrics;

Aim 2: assess the effects of CHEF-WPM at a community level across process (feasibility, usage, acceptability, satisfaction), preliminary efficacy (motivation, opportunity, ability, household food waste), and exploratory (sustainable dietary behaviors) metrics.

It is valuable to study outcomes from both online exposures to the videos and outcomes from a more intensively implemented community-level delivery to gain insights into the effects of different types of deployment. Such insights could shape future motivation–opportunity–ability-oriented efforts using these or other videos.

## 2. Methods

The evaluation will explore the effects of the program through two distinct investigations, namely (1) when the intervention content is accessed voluntarily in a population-based setting (population CHEF-WPM) and (2) when the intervention content is accessed through intensive delivery as part of a remote class in a community setting (community CHEF-WPM). The population CHEF-WPM investigation will include two types of evaluations, and the community CHEF-WPM will include one type of evaluation. The subsequent sections in this report, as applicable, will be divided into the following three sections for clarity: *Population Intervention 1*, *Population Intervention 2*, and *Community Intervention*. This protocol is reported in accordance with SPIRIT (Standard Protocol Items: Recommendations for Interventional Trials) guidance. A completed SPIRIT checklist is available in Additional File 1. Additionally, Table 1 displays an overview of the objectives and methods for the three distinct evaluation components of the CHEF-WPM intervention.

### 2.1. Intervention

The overall goal of the CHEF-WPM intervention is to increase consumers’ motivation, perceived opportunity, and ability to reduce food waste using home-based culinary techniques. The intervention will include eight modules, each containing three to five brief (4–8 min) videos, as well as downloadable recipes and worksheets. CHEF-WPM is designed to be used *a la carte* or as a self-paced online course.

The eight module topics include:My whole plate: Meal Planning & Kitchen Management with a ‘No Food Waste’ Lens;Veggies: Roots to Stem;Fruit: Fresh or Bruised;Meat- & Plant-Based Proteins;Fish & Seafood: Sear It, Don’t Fear It;Bread, Grains, Snacks, Sweets;Cooking Liquids & Dairy;Leftovers Are My Jam.

Each module focuses on improving the *motivation*, *opportunity*, and *ability* to reduce food waste using home-based culinary techniques. The modules will highlight *motivations*, including saving money, avoiding waste, confidence, setting an example for children, and improving nutrition, pleasure, and environmental benefits. The modules will also focus on perceived *opportunity* and illustrate ways to shift contextual factors, such as time and schedule, kitchen arrangement and food storage, and technologies, among other aspects. *Ability* will be addressed via sharing techniques, recipes, and tricks to prevent and minimize food waste at home and problem-solving strategies for challenges to food waste prevention. Adapted from the work of ölander and ThØgersen [11], Figure 2 displays the conceptual framework guiding the CHEF-WPM program.

The content will be developed and filmed at Drexel’s College of Nursing and Health Professions’ Food and Hospitality Management Space, and in the kitchen studio of the food-waste educator. The developed content will be hosted on a freely accessible website, Kajabi (http://kajabi.com; accessed on 1 July 2024). The CHEF-WPM program will be built and delivered to key audiences as an online course on Kajabi. Kajabi is an “all-in-one” platform that we will use to build our program, engage with learners (participants), and collect feasibility and preliminary efficacy metrics. The videos will also be disseminated via social media (i.e., X [FKA Twitter], Instagram, TikTok) and through partnerships with food-security organizations, retailers, nutrition education programs, and others.

### 2.2. Population Intervention 1

#### 2.2.1. Overview

The evaluation of Population Intervention 1 will use a single-arm post-test only study design. All home cooks who access the videos will be invited to answer a brief post-video survey about acceptability and satisfaction (*n* = 1068).

#### 2.2.2. Study Population and Recruitment

Potential participants will be 18 years or older, responsible for at least half of their household food preparation, prepare meals at home at least twice each week, have access to the internet, and understand English. The following groups will be excluded: adults unable to consent, individuals who are not yet adults (infants, children, and teenagers), and prisoners. Participants will be recruited through Drexel Food Lab networks and in partnership with community and national organizations. Recruitment methods will include digital and paper advertisements, email advertisements, QR codes, and other methods, such as shelf-tags at local libraries. QR codes and email links will direct individuals to the CHEF-WPM videos. At the end of each video, the viewers will have the opportunity to “opt-in” to complete a short survey to assess satisfaction, engagement, and comprehension. Our goal is to recruit a minimum of 1068 individuals to participate in that brief survey, providing 95% power to detect an effect size of 0.3. However, we will collect and analyze data from all of the participants who complete the 5-question survey. In other words, *we will not cease recruitment* once we obtain a sample size of 1068 quality answers.

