#### 2.3.2. Study Population and Recruitment

The inclusion and exclusion criteria are the same for both population-level interventions. Potential participants should be 18 years or older, responsible for at least half of their household food preparation, prepare meals at home at least twice each week, have access to the internet, and understand English. The following groups will be excluded: adults unable to consent, individuals who are not yet adults (infants, children, and teenagers), and prisoners.

We will recruit participants for this evaluation by utilizing ResearchMatch and Build Clinical. ResearchMatch is a website that connects potential participants with researchers by emailing individuals with a recruitment message that explains the basic details of the research study. If individuals are interested in participating in the study, they will be directed to a screening questionnaire. Build Clinical will run an online advertisement campaign on online and social media websites, such as Facebook, Instagram, and X (formerly Twitter). When individuals press on these digital advertisements, they will be redirected to a landing page where they can learn more about the study and fill out a screening questionnaire.

If the interested individual from either platform is eligible for the study, a research assistant will call the individual and further explain the goals and procedures of the intervention. After this phone call, the research assistant will send the individual an email with a link to the information sheet for exempt research. Proceeding to the survey will serve as a proxy for written consent. Participants will be offered a USD 10 incentive for completion of the pre- and post-video surveys, and an additional USD 5 incentive for completion of each follow-up assessment (3 and 6 months; USD 10 for completion of both; USD 20 for completion of the entire study).

A sample size of 500 is sufficient to provide 95% power to detect an effect size of 0.43. Participants will be purposively sampled by age, race/ethnicity, gender, and income to optimize the diversity of our sample. Our goal is for our sample to mirror the US census demographic composition of the most recent census (Gender—Male: 49.6%, Female: 50.4%, Non-binary: natural fallout; Race—White: 76%, Black/AA: 14%, Asian or Pacific Islander: 6%, American Indian/Alaskan Native/Other: 2%; Hispanic Ethnicity—Hispanic: 19%, Non-Hispanic: 59%).

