#### 2.3.3. Data Collection and Outcomes

A structured survey (~10-min pre-post survey) will evaluate specific educational videos across process (feasibility, usage, acceptability, and satisfaction) and preliminary outcome (motivation, opportunity, and ability) metrics. The enrolled participants will also complete 3- and 6-month follow-up surveys. The structured survey will ask about demographic characteristics and will obtain baseline information about motivation, opportunity, and ability as they relate to food-waste prevention. The survey will also contain three embedded food-waste prevention videos for the participants to view. After viewing each video, the participants will be asked to answer questions about the content to assess video satisfaction, engagement, recall, and comprehension of information, in addition to questions about motivation, opportunity, and ability. The 3- and 6-month follow-up surveys will primarily focus on motivation, opportunity, and ability to reduce household food waste.

#### 2.3.4. Data Analyses for Population Interventions 1 and 2

Descriptive characteristics of our study sample will be calculated as means ± standard deviations, frequencies, chi-square contingency analyses, and standardized residuals, unless otherwise noted. Changes in motivation, opportunity, and ability will be analyzed as continuous or categorical variables. Mixed factorial analyses of covariance (ANCOVA) with repeated measures will be used to determine whether mean differences exist in participant satisfaction, engagement, and comprehension after controlling for the influence of socio-demographic- (age, race and ethnicity, marital status, education, and income) and household-related characteristics measured at baseline. Differences will be estimated for all categorical variables using McNemar’s exact significance probability testing for paired nominal data. All quantitative statistical analyses will be accomplished using IBM SPSS Statistics.

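### The power statement for Population Intervention 1 does not reproduce: 1068 respondents are not what 95% power at an effect size of 0.3 requires, and the figure matches a ±3-point margin of error instead

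*Protocol article*

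**What the plan says.** Section 2.2.2 (Study Population and Recruitment) of the protocol article gives the sample size for the brief post-video survey as "a minimum of 1068 individuals to participate in that brief survey, providing 95% power to detect an effect size of 0.3". The same section makes 1068 a floor: recruitment continues beyond it and all completed surveys are analysed.

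Section 2.2.1 describes the design: "The evaluation of Population Intervention 1 will use a single-arm post-test only study design". Table 1 repeats this. After each video, viewers may opt in to "complete a short survey to assess satisfaction, engagement, and comprehension".

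Section 2.3.4 covers the analysis of both population evaluations. It lists chi-square contingency analyses and then says: "Mixed factorial analyses of covariance (ANCOVA) with repeated measures will be used to determine whether mean differences exist in participant satisfaction, engagement, and comprehension", with adjustment for socio-demographic and household characteristics.

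For the companion evaluation, Section 2.3.2 says: "A sample size of 500 is sufficient to provide 95% power to detect an effect size of 0.43".

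The article gives no alpha, sidedness, effect-size metric, reference value or comparison for the 0.3.

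**The concern.** The sentence names a sample size, a power and an effect size. Those three should fit together under some test that the design allows, and under the ordinary candidates they do not.

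The design adds a second difficulty. With one arm, one measurement and no stated benchmark, there is no contrast that isolates an effect of the videos, so it is unclear what the 0.3 refers to.

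This sentence is the article's only justification for the largest of its three samples (1068 against 500 and 60 in Table 1), and Aim 1 is worded in terms of effects. A results paper that carries the sentence over would credit an opt-in survey with a power property that the article does not establish.

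**Working it through.** **Inputs.** From Section 2.2.2: n = 1068, power 95%, effect size 0.3. Assumed because not stated: two-sided alpha 0.05, standardised effect (SD = 1), equal groups where there are two, no dropout. The normal quantiles are 1.960 and 1.645, and (1.960 + 1.645)² = 12.995.

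**Step 1. Try to reproduce 1068.**

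- One sample: n = 12.995 / 0.3² = 144.4, so 145. The t-test version gives 146.3, so 147.
- Two equal groups: n per group = 2 × 12.995 / 0.3² = 288.8, so 289 (578 in total). The t-test version gives 289.7, so 290 (580 in total).

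Other readings of the effect size, also at 95% power:

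| Reading of 0.3 | Total n |
|---|---|
| One-sided test, one sample | 121–122 |
| One-sided test, two equal groups | 482–484 |
| Correlation r | 139 |
| Chi-square w, 1 to 20 df | about 144–341 |
| ANOVA f, 2 to 40 groups | about 146–463 |
| Regression f², 1 to 20 predictors | about 45–119 |
| Risk difference of 0.30 | 104–140 |

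None is near 1068.

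**Step 2. Find settings that do come near.**

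- Two unequal subgroups split 16/84 at d = 0.3: n = 12.995 / (0.3² × 0.16 × 0.84) = 1074.
- Two equal groups at alpha 0.001: 1084.
- ANOVA with f = 0.15 and 10 groups: 1057.

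The article states none of these settings.

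**Step 3. What 1068 would deliver at 0.3.**

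- Power, one sample: 0.3 × √1068 − 1.960 = 7.84, which is above 99.99%.
- Power, two groups of 534: 0.3 × √(534/2) − 1.960 = 2.94, which is 99.8%.
- Effect detectable with 95% power: 3.605 / √1068 = 0.11 (one sample), or 3.605 × √(2/534) = 0.22 (two equal groups).

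**Step 4. Compare with a margin of error.**

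- n for a 95% confidence interval of ±3 points at p = 0.5: 1.96² × 0.25 / 0.03² = 0.9604 / 0.0009 = 1067.1, rounded up to 1068. The match is exact.
- Half-width at 1068: 1.96 × 0.5 / √1068 = 0.02999, or 3.0 points.

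**Step 5. Cross-check with Population Intervention 2.** At n = 500 the half-width is 1.96 × 0.5 / √500 = 0.0438, or 4.38 points, against a stated effect size of 0.43. The digits are close but not exact: ±4.3 points would need 0.9604 / 0.043² = 519.4, so 520. The effect detectable at 95% power with 500 is 0.16 (one sample) or 0.32 (two equal groups).

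**The case against.** Section 2.3.4 does plan comparisons for this survey. Chi-square tables and adjusted mean differences in satisfaction, engagement and comprehension can be computed from post-test data alone. Subgroup differences have effect sizes, and a split of about 16/84 would need close to 1068. A reader might infer from the single-arm design that no effect of any kind can be tested. The documents do not support that: only an intervention effect is out of reach. This part of the objection stands. It does not rescue the sentence, because the article ties the 0.3 to no subgroup, split or contrast.

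The margin-of-error origin is not documented either. No derivation is shown, the match needs 0.03 to have become 0.3, and the pair for Population Intervention 2 fits only loosely. A reader might take the relabelling as established; it is an inference, though a well-supported one. The failure to reproduce does not depend on it.

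The practical harm is also limited. Section 5.3 calls this a feasibility study ahead of an adequately powered randomised trial, 1068 is only a minimum, and the survey is described as one of acceptability and satisfaction. The alpha and test may sit in a fuller protocol. All of this lowers the stakes. The printed statement still needs correcting, because its three numbers do not fit together under any setting that the article gives.

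**Conclusion.** The power statement is wrong as written. Under two-sided alpha 0.05, which is assumed, 95% power at 0.3 needs 147 (one sample) or 580 (two equal groups), so the stated n is about 7.3 or 1.8 times the requirement, depending on the comparator. The larger ratio belongs to the one-sample case only and should not be quoted alone.

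A reader might infer that the survey is underpowered or the target too low. The opposite holds for these standard cases: 1068 exceeds what they need at 0.3. The defect lies in the justification, not in the recruitment target.

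What 1068 supports directly is precision: a half-width of at most 3.0 percentage points for a proportion pooled over videos. That assumes independent answers from different people. It covers sampling error only and says nothing about how opt-in viewers differ from other home cooks.

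**What to change.** Replace the power sentence in Section 2.2.2 with wording such as: *1068 unique respondents give a 95% confidence interval with half-width of at most 3.0 percentage points for any proportion pooled over videos (worst case 50%), reflecting sampling error only and not opt-in selection.* The word unique matters because the survey is offered after every video and Section 2.2.2 counts both individuals and answers.

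Add that Population Intervention 1 tests no intervention effect and that its subgroup comparisons under Section 2.3.4 are exploratory.

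If a power claim is preferred, name the contrast, the group split or reference value, the alpha and the effect-size metric, and restate the figure to match.

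The cost is a few lines of text and a less favourable-sounding claim. Recruitment and data collection are unchanged.
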